#### Adherence and determinants of adherence

##### Adherence

Throughout the study period, adherence to the key components of each prevention strategy will be measured for all care providers on the basis of the medical records of all the pregnant women. During the pre-test, adherence to the current Dutch guideline will be measured, and adherence to the allocated prevention strategy will be measured during the post-test. The key components are: assessment of the clinical risk factors for EOGBS, culture-taking during pregnancy and during labour, IAP during labour and treatment of the baby. In this way, the level of adherence will be measured as the proportion of all prescribed activities the professional has actually applied: “completeness of use”. The medical record search will be performed using standardised registration forms. Only the combination strategy requires a recto-vaginal culture to be taken from pregnant women between 35 and 37 weeks by their care provider. In all prevention strategies the care provider decides whether IAP is necessary or where there is a contra-indication for antibiotic prophylaxis.

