## Background

Vertical transmission of the group B haemolytic streptococcus (GBS) during delivery is the main cause of neonatal infection in the first week of life and it leads to early-onset Group B haemolytic streptococcus disease (EOGBS). EOGBS is an important cause of perinatal mortality, serious illness and long-term effects for the baby [1,2]. The mortality rate for children with EOGBS varies from 9.0 to 10.3% [3-5].

Estimates of the incidence of EOGBS vary between 0.23 and 1.22 per 1000 live births in several European countries and the USA [6-14]. The estimated incidence of EOGBS in the Netherlands is based on proven (0.36 per 1000 live births) [13] and probable EOGBS cases and is 1.9 per 1000 live births [1].

Because of the severe consequences, the importance of the prevention and mitigation of EOGBS is widely recognised. Primary prevention of EOGBS is possible with intra-partum antibiotic prophylaxis (IAP) for pregnant women who are GBS carriers. Different prevention strategies are used internationally based on identifying mothers at risk, either by screening for maternal colonisation with GBS during pregnancy or by identifying risk factors for EOGBS in pregnancy or during labour. Established risk factors include the pre-labour rupture of membranes (> 18 hours), intra-partum fever (≥38.0°C), preterm birth (<37 weeks), GBS bacteriuria in current pregnancy and a previous sibling with EOGBS.

However, none of the preventive EOGBS strategies in place at present result in the complete prevention of EOGBS, either because the strategy is not fully effective in itself, or because it has drawbacks which may result in non-adherence by both care providers and pregnant women.

1. In the risk-based strategy, all women with one or more of the established risk factors for EOGBS receive IAP. Care providers are clear about how to apply this strategy. The effect of the strategy is limited because over 40% of babies who develop EOGBS are born to mothers without a risk factor during pregnancy or labour [13].

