2. In the screening strategy, a culture is taken at 35–37 weeks of gestation, and all GBS-colonised women receive IAP. As with the risk-based strategy, care providers understand clearly how to apply this strategy, which is affected by two problems: 1. the failure of the laboratory to detect GBS in pregnant women accurately accounts for a consistent proportion of EOGBS cases [6,15-18] and 2. the large numbers of women receiving IAP and the possible negative side-effects such as antibiotic resistance [6].

3. In the combination strategy, a culture is taken at 35–37 weeks of gestation and women with both GBS colonisation and one or more of the established risk factors for EOGBS receive IAP. This strategy leads to the most accurate use of IAP and therefore results in the lowest rate of negative side-effects. However, persistent problems are that laboratories fail to detect GBS in pregnant women accurately [6,15-18] and over 40% of babies who develop EOGBS are born to mothers without a risk factor during pregnancy or labour [13]. Furthermore, adherence to this strategy may be affected by awareness among care providers and pregnant women of GBS colonisation and this could lead to an increase in IAP, even in the absence of risk factors.

4. The current Dutch guideline, which was issued in 1998 [19], prescribes IAP for women with intra-partum fever, a previous sibling with EOGBS or GBS bacteriuria during current pregnancy. Cultures are taken in cases of pre-labour membrane rupture or preterm birth and IAP is given if GBS colonisation is established. One of the problems with the Dutch guideline is that culture results take up to 72 hours to deliver and cultures are therefore often not yet available when labour starts. IAP in response to a risk factor is therefore predominantly based on clinical observation. The problems mentioned above – the inaccurate detection of GBS in the combination strategy [6,15-18] and the fact that over 40% of babies who develop EOGBS are not born to mothers with risk factors [6]– are also applicable to the Dutch guideline. 

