## Discussion

The effective prevention of EOGBS will be the product of the efficacy of the applied prevention strategy (to what extent can the strategy in itself prevent EOGBS) and the level of implementation (to what extent is the strategy adhered to by all care providers and all pregnant women). Since improved adherence may enhance EOGBS prevention, our study focuses on determinants that affect adherence to three prevention strategies in daily practice. The empirical data about adherence will be used to assess the cost-effectiveness of each strategy in daily practice.

Although the results will primarily be used for the national implementation of the most cost-effective strategy in the Netherlands, the results could be of interest to health-care professionals, policymakers and insurance companies in other countries. Regardless of the prevention strategy used, we expect that other countries will also have problems with actual adherence. Our determinant analysis found a variation in adherence to several recommendations of the guideline, especially in the assessment of clinical risk factors and culture-taking procedures. In the United Kingdom also, considerable variation in the management of EOGBS risk prevention was recently reported, including the application of risk factors and the choice of antibiotics [35].

Our study has some limitations. Due to the low prevalence of EOGBS, a clinical effect study for the detection of a statistically significant difference in the prevalence of EOGBS is not feasible. Our study will use the incidence of neonatal colonisation as a proxy measure for implementation. A second limitation is that the results may be affected by regional variations. To overcome this problem we will include regions with minimal differences in the organisation of maternity care (OCGs) and population characteristics.

We expect the results of our study to contribute significantly to the national and international re-evaluation of the best strategy for the prevention of EOGBS.

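### The pooled adherence percentage can stay high when indicated IAP is not given, and it is not like-for-like between strategies or between pre-test and post-test

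*Protocol article*

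**What the plan says.** The Adherence section (protocol article, Activity 2) lists the components as "assessment of the clinical risk factors for EOGBS, culture-taking during pregnancy and during labour, IAP during labour and treatment of the baby". It then brings them into one figure: "the level of adherence will be measured as the proportion of all prescribed activities the professional has actually applied". It does not say how components are weighted, or whether the proportion is formed over activities, per woman or per provider. The same section also states that "adherence to the key components of each prevention strategy will be measured for all care providers".

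The strategies do not prescribe the same activities. On antenatal culture: "Only the combination strategy requires a recto-vaginal culture to be taken from pregnant women between 35 and 37 weeks by their care provider". On IAP, the Background gives two different rules: "In the risk-based strategy, all women with one or more of the established risk factors for EOGBS receive IAP", whereas under the combination strategy "women with both GBS colonisation and one or more of the established risk factors for EOGBS receive IAP". The yardstick is the Dutch guideline in the pre-test and the allocated strategy in the post-test.

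The Sample size section sets 315 women per strategy, for a 95% interval of 65–75% at 70% adherence and for a 10-point difference between strategies (alpha 0.05, power 80%). The Analysis section takes pre-test to post-test differences in the outcome percentages into the cost-effectiveness analysis. The Discussion adds: "The empirical data about adherence will be used to assess the cost-effectiveness of each strategy in daily practice".

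**The concern.** A share of all prescribed activities is governed by whichever activities are prescribed most often. Each strategy's IAP rule refers to risk factors, so assessment applies to every woman. The antenatal culture applies to every woman in one region only. IAP, which the Background names as the means of primary prevention, applies only to women who meet a rule. This has two consequences.

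- **Masking.** A region could omit much of its indicated IAP and still show a high level of adherence. The combination score is the least sensitive, because that strategy adds an item for every woman and has fewer IAP indications than the risk-based strategy.
- **Comparability.** Equal practice on each activity gives different scores in different regions, because the mix of activities differs. The same happens over time in the two regions that change strategy after the pre-test.

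The Background treats the impact of a strategy as its efficacy multiplied by its level of implementation, and the study is meant to replace the earlier model's assumption of 100% adherence. An adherence figure driven by item mix would be a poor basis for comparing strategies or for that replacement.

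**Working it through.** **1. The plan's own figure.** With n = 315 and p = 0.70, 0.70 ± 1.96·√(0.21/315) = 0.70 ± 0.051, or 64.9–75.1%. The stated 65–75% reproduces. For 70% against 80% (two-sided 0.05, power 80%), 294 per group are needed without and 313 with continuity correction, so 315 fits the corrected form. Both calculations treat adherence as one yes/no result per woman, which is not the same quantity as a proportion of activities.

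**2. Inputs for the masking check.** From the document: the components, the culture rule and the IAP rules. Not in the document, so assumed: share of women with a risk factor r = 20% (range 10–30%); carriage g = 20%; assessment items per woman k = 1, or 5 if each risk factor is counted; no baby item.

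**3. Pooled score with no indicated IAP given and all else done.**

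- Risk-based: k/(k + r). Central case 1/1.20 = 83.3%; with k = 5, 5/5.20 = 96.2%. Extremes: 1/1.30 = 76.9% and 5/5.10 = 98.0%.
- Combination: (k + 1)/(k + 1 + r·g). Central case 2/2.04 = 98.0%; with k = 5, 6/6.04 = 99.3%. Extremes: 2/2.06 = 97.1% and 6/6.02 = 99.7%.
- Dutch guideline: (k + c)/(k + c + d + c·g), with c the share needing a culture (assumed 10–30%) and d the share with a direct IAP indication (assumed 2–5%): about 92–99%.

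Counting one baby activity per woman as done raises the central scores to 2/2.20 = 90.9% (risk-based) and 3/3.04 = 98.7% (combination).

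**4. Does the pooling unit matter?** Central case, no IAP given:

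| Scoring | Risk-based | Combination |
|---|---|---|
| Pooled over activities | 83.3% | 98.0% |
| Averaged per woman | 0.8·1 + 0.2·(1/2) = 90.0% | 0.96·1 + 0.04·(2/3) = 98.7% |
| All-or-nothing per woman | 80.0% | 96.0% |

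Each figure lies above the 70% planning value.

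**5. Comparability.** Give all regions the same performance on each activity: assessment 95%, culture 80%, IAP 60% (r = g = 20%, c = 15%, d = 5%, k = 1; all assumed).

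- Risk-based: (0.95 + 0.20·0.60)/1.20 = 89.2%.
- Combination: (0.95 + 0.80 + 0.04·0.60)/2.04 = 87.0%.
- Dutch guideline: (0.95 + 0.15·0.80 + 0.08·0.60)/1.23 = 90.9%.

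With culture-taking at 50%, the scores are 89.2%, 1.474/2.04 = 72.3% and 1.073/1.23 = 87.2%. Risk-based and combination then differ by about 17 points from activity mix alone. A region moving from the Dutch guideline to the combination strategy would fall by about 15 points (87.2 to 72.3) with no change in performance on any activity.

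**6. Precision of the IAP component.** The risk-based region has 315·0.20 = 63 indicated women: 1.96·√(0.21/63) = ±11 points at 70% adherence. The combination region has 315·0.04 = 12.6, about 13: 1.96·√(0.21/13) = ±25 points.

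**The case against.** Five points deserve a fair hearing.

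- **The article is condensed.** Scoring rules and component tables usually sit in the full protocol or analysis plan. That stands as far as missing weights go, and their absence is not the point here. The article does state a rule for the level of adherence, and it sizes the comparison on one adherence percentage. The weakness lies in that rule.
- **Missed IAP is not invisible.** A reader might infer that the plan rests on a single equally weighted score and cannot see omitted IAP. The document does not support this. Equal weighting is the plain reading, not stated text; adherence to the key components is said to be measured; and IAP is taken from the medical records as a clinical outcome. What remains is that the article defines the level of adherence by the pooled proportion, and does not name IAP adherence among indicated women as a figure to be compared or modelled.
- **The model input is not specified.** A reader might infer that the pooled score enters the cost-effectiveness model. No section says so: the text speaks of empirical data, of data about adherence and of outcome percentages in the plural. Bias in the model is therefore a risk to exclude, not an established fault.
- **Cultures are part of prevention.** Under the combination strategy a missed culture is a real failure, and a lower score then answers the research question on adherence. This stands. With culture-taking at 80% the three scores in the example lie within 4 points; the 17-point gap needs half of the cultures to be missed.
- **IAP adherence alone is no substitute.** A woman whose culture or assessment was missed cannot be shown to meet the rule and drops out of the denominator, so a region with few cultures could look perfect. The figure might also rest on about 13 women. This stands and shapes the fix.

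**Conclusion.** The concern holds in limited form. The stated definition lets activities prescribed for every woman dominate, so the percentage can remain high when indicated IAP is not given, and it does not measure the same thing across strategies or, in the two regions that change, across periods. Under the assumed shares of 20% the score with no indicated IAP is about 83% (risk-based) and 98% (combination), with ranges of about 77–98% and 97–99.7% over the inputs shown. These sizes depend on shares the document does not give and on a deliberately extreme scenario, total omission of indicated IAP with everything else done. The direction does not depend on the pooling unit: all three scoring methods give 80% or more in the central case. The finding concerns how adherence is summarised and compared. It does not show that missed IAP would go unrecorded or that the cost-effectiveness model is wrong.

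**What to change.** In the Adherence section, report adherence by component, each with its own denominator and interval:

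- risk-factor assessment: all women;
- culture: women for whom the allocated strategy requires it, with a required culture not taken counted as a failure;
- IAP: women meeting the allocated strategy's IAP rule;
- treatment of the baby: babies for whom the strategy prescribes it.

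Beside the IAP component, show the number of women whose indication could not be determined because an assessment or culture was missed. Use the component figures together, not the pooled percentage and not IAP alone, to compare strategies and as inputs to the cost-effectiveness model. Keep completeness of use as a descriptive summary with its pooling unit stated, and say in the Sample size section which quantity the 315 refers to.

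The cost is wording and a few more tables from records that are to be abstracted anyway. The real downside is that the ±5-point precision does not carry over to IAP: expect about ±11 points (risk-based) and ±25 points (combination) at 70% adherence under the assumptions above, and the text should say so.

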#### Sample size

To determine adherence to each strategy with sufficient precision, 315 women are needed (in the case of 70% adherence, the 95% confidence interval will be 65-75%) since this number will ensure statistical significance at a variation in adherence of 10% between strategies (alpha = 0.05, power = 80%).

The pre-test must include 105 pregnant women per region: 315 in total for the three regions. The post-test must include 315 pregnant women per region: 945 in total for the three regions.

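### The adherence score counts omitted activities but not IAP given outside the strategy's rule, and it is not the per-woman proportion that the sample size describes

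*Protocol article*

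**What the plan says.** Under Activity 2, the Adherence section lists the key components as "assessment of the clinical risk factors for EOGBS, culture-taking during pregnancy and during labour, IAP during labour and treatment of the baby". Adherence to them "will be measured for all care providers on the basis of the medical records of all the pregnant women", and "the level of adherence will be measured as the proportion of all prescribed activities the professional has actually applied". The article calls this completeness of use.

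The Background (item 3) gives the combination rule: "women with both GBS colonisation and one or more of the established risk factors for EOGBS receive IAP". It presents accurate use of IAP as the strategy's advantage. It then warns that adherence may suffer once carriage is known, because "this could lead to an increase in IAP, even in the absence of risk factors".

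The Sample size section reasons in women: "To determine adherence to each strategy with sufficient precision, 315 women are needed", and "in the case of 70% adherence, the 95% confidence interval will be 65-75" percent. It also claims 80% power at alpha 0.05 for a 10% difference between strategies.

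On who decides about IAP, the Adherence section adds: "In all prevention strategies the care provider decides whether IAP is necessary or where there is a contra-indication for antibiotic prophylaxis".

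**The concern.** Adherence is research question (a) and the basis of the sample size, and the Discussion says the adherence data will be used to assess cost-effectiveness. Three features of the text do not fit together.

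- **Direction of error.** A strategy's rule on IAP can be broken by withholding IAP that is indicated or by giving IAP that is not. The stated ratio sees only the first. The second is the failure that the Background itself raises for the combination strategy, and raises as a matter of adherence.
- **Unit.** The score is a share of activities, measured for care providers. The sample size describes a share of women.
- **Reference standard.** IAP can be scored only against a rule. The Background states rules, whereas the Adherence section leaves necessity to the provider.

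At stake is whether the answer to question (a) can be read as how far each strategy was followed, and whether the quoted precision belongs to that answer.

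**Working it through.** **1. What the score can register.** Let P be the number of prescribed activities, A the number of those applied, and U the number of women given IAP outside the rule. The defined score is A/P. An omission lowers A. U appears in neither A nor P, so the score is the same for every value of U. If A = P, it is 100% however large U is.

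**2. Reproducing the sample-size figures.** Inputs from the Sample size section: p = 0.70, n = 315, alpha 0.05 (taken as two-sided, which is not stated), power 80%, difference 10 points.

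- Half-width = 1.96 × sqrt(0.70 × 0.30 / 315) = 0.0506, giving 64.9% to 75.1%. This matches the stated 65-75%.
- 70% versus 80%: n = [1.96 × sqrt(2 × 0.75 × 0.25) + 0.842 × sqrt(0.21 + 0.16)]² / 0.10² = 294 per group, or 313 with continuity correction. Power at 315 is 82.8%.
- 70% versus 60%: n = 356 (376 corrected), and power at 315 is 75.0%.

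The stated figures therefore come out, with 70% against 80%, as a simple comparison of proportions with one yes/no result per woman.

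**3. The same 315 women under the activity-share score.** Assume m = 2 to 5 prescribed activities per woman, 70% of them applied, and within-woman correlation ρ. Then half-width = 1.96 × sqrt(0.21 × [1 + (m − 1)ρ] / (315m)).

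| m | ρ = 0 | ρ = 0.3 | ρ = 1 |
|---|---|---|---|
| 2 | 3.6 points | 4.1 | 5.1 |
| 5 | 2.3 points | 3.4 | 5.1 |

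Before any clustering by provider, the interval is as wide as stated or narrower. The mismatch concerns which quantity the figures describe, and it is not evidence of too small a sample.

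Converting to a yes/no by requiring every activity would move the quantity away from 70%. At 70% per activity and independence, it is 0.7² = 49% for two activities and 0.7⁵ = 17% for five.

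**4. How much unindicated IAP could go unseen.** The article gives no carriage or risk-factor rates. Assume carriage g = 15-25%, at least one risk factor in r = 10-30%, independence of the two, and IAP in a fraction x = 10-100% of carriers without a risk factor.

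- IAP indicated: 315 × g × r = 4.7 (0.15, 0.10) to 23.6 (0.25, 0.30).
- IAP not indicated but given: 315 × g × (1 − r) × x = 3.3 (0.15, 0.30, x = 0.10) to 70.9 (0.25, 0.10, x = 1).
- Women with a correct IAP decision, if no indicated IAP is missed: 1 − 3.3/315 = 99.0% down to 1 − 70.9/315 = 77.5%. The defined score can be 100% throughout.

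Independence is a simplification. GBS bacteriuria is both a listed risk factor and a sign of carriage, so the two overlap. Independence therefore understates the indicated group and overstates carriers without a risk factor. These figures show scale and are not estimates.

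**5. Who defines indicated.** If the provider's own judgement defines necessity, withheld IAP was not necessary and extra IAP was. Neither can then count as a departure. If the Background's rules define it, both can. The article does not say which reading governs the scoring.

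**The case against.** The best defence is that the information is not lost. The section on outcomes in women and babies collects risk factors, culture results and IAP from the records. The costs section updates the decision model with the study's empirical data, and the Analysis section carries outcome percentages into the cost-effectiveness analysis. Extra IAP can therefore be seen and costed even though the adherence score ignores it. This stands, and it limits the point to the definition of adherence. It does not rescue that definition, because those items are listed as clinical outcomes and nothing in the article counts unindicated IAP as non-adherence.

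Four stronger readings might be inferred, and the document does not support them.

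- **Cost-effectiveness is biased in favour of the combination strategy.** The sections just named let observed IAP enter the model, so any bias depends on how the model is fed. The score also ignores over-use in all three regions, and only the combination strategy adds a culture at 35-37 weeks that can be omitted. The net direction between strategies is unknown.
- **Risk-factor assessment will swamp IAP in a pooled score.** No pooling or weighting rule is stated, and the reference to key components allows results by component.
- **315 women are too few.** Step 3 shows otherwise for the unit mismatch.
- **The 5-point precision is claimed for women with IAP indicated.** The Sample size section makes no such claim. With as few as 5 such women, the normal-approximation interval would not be usable anyway.

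The Background also says only that extra IAP could happen. It does not forecast it. Finally, the provider-discretion sentence can be read as ordinary judgement within a strategy. That is a fair reading, but scoring needs the reading to be stated.

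**Conclusion.** The point holds in a limited form. As defined, adherence cannot fall when IAP is given outside the allocated strategy's rule, although the article itself treats that as a threat to adherence under the combination strategy. This follows from the definition and needs no assumption. Its size does: on the assumed rates, about 3 to 71 of 315 women, or 1% to 23%, could be treated outside the rule with no effect on the score.

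Separately, the 65-75% interval and the 80% power describe a per-woman binary measure near 70%, which the Adherence section does not define. The consequence is that the precision is attached to the wrong quantity. Neither a shortage of women nor a biased cost-effectiveness result has been shown. A fuller protocol may refine the definition, but the one published here is explicit and gives a partial answer to question (a).

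**What to change.** 1. Reconcile the statement on provider decision with the IAP rules in the Background, so that there is one written standard for scoring. Which reading is right is for the investigators to settle.
2. Add a per-woman yes/no IAP-decision measure: IAP given if and only if indicated under the allocated strategy, with the woman's refusal and contra-indication coded separately. Analyse it with n = women.
3. Report under-use (among women with IAP indicated) and over-use (among women without an indication) for each strategy, each with its own denominator and an interval suited to small numbers. This is needed because the per-woman measure is dominated by women with no indication. In the illustration, missing every indicated case in the combination region would lower it by only 4.7/315 = 1.5 to 23.6/315 = 7.5 points.
4. Keep completeness of use, reported by component. Avoid a single all-or-none score across steps, because it depends heavily on how many steps a strategy has.
5. Enter both under-use and over-use in the cost-effectiveness model.
6. State that the 65-75% interval and 80% power apply only to a per-woman binary measure near 70%, and not to the activity share or the subgroup with IAP indicated. If the new measure is expected to lie elsewhere, recompute.

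The cost is a re-definition and a little more programming. Risk factors, cultures and IAP are already to be collected. The registration forms are not shown, so codes for refusal and contra-indication may have to be added. The reported adherence figure may be lower.
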